**Preliminary Research**

Our preliminary studies demonstrate our expertise in conducting research with oral nicotine products, including remote clinical trials and naturalistic switching studies. Our preliminary research also highlights our expertise conducting research with rural Appalachian populations.

Qualitative assessment of ONPs among rural Appalachian adults who smoke. [name] conducted focus groups assessing perceptions of ONPs among adult smokers living in Appalachia. Participants perceived ONPs to be lower risk than cigarettes but to be similarly addictive. Participants also noted that ONPs seemed to be “cleaner,” more discreet, and more socially acceptable. Conclusions: rural Appalachian adults who smoke were open to using ONPs and held perceptions that might support switching.

Abuse liability assessment of ONPs among rural Appalachian adults who smoke. Drs. [name] and [name] collaborated on a pilot randomized cross-over study assessing nicotine pharmacokinetics and subjective effects of ONPs with different nicotine concentrations. In 3 separate visits, N=30 adult smokers from Ohio Appalachia used a 3mg nicotine concentration ONP, 6mg nicotine concentration ONP, or a usual brand cigarette following a standardized use protocol. Participants reported that ONPs were moderately appealing and noted similar overall withdrawal relief across products. Plasma nicotine peaked highest and earliest when smoking a cigarette but using the 6mg ONP resulted in greater plasma nicotine levels than the cigarette from 30-60 minutes of follow-up. Conclusions: (1) The higher nicotine concentrations available in ONPs (than in NRT) support greater plasma nicotine delivery. (2) ONPs relieve withdrawal symptoms and are moderately appealing to rural Appalachian adults who smoke.

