# **2. Objectives**

**Primary Objectives and Outcome Measures**

This study will be carried out in a group of adults (≥21 years old) cigarette smokers (n=1000) from rural Appalachian regions of the United States according to the following aims.

**Aim 1:** Evaluate short-term changes in cigarette smoking patterns, including switching, abstinence from cigarettes, and frequency of smoking between ONPs and NRT. At the conclusion of the Switch Phase, the highest rates of (H1a) complete switching (cigarette abstinence + study product use) and (H1b) abstinence from cigarettes will occur in the ONP group. H1c: ONP participants will smoke the fewest cigarettes per day.

**Aim 2:** Compare product appeal, craving, withdrawal relief, and perceived cigarette dependence between ONPs and NRT. Participants randomized to ONPs will report (H2a) greater product appeal and (H2b) greater reduction in craving and withdrawal symptoms than participants randomized to NRT. H2c: Among complete switchers, ONP participants will report greater reductions in cigarette dependence than NRT participants.

**Aim 3:** Examine sustained changes in tobacco use behaviors, including abstinence from cigarettes, purchase of ONPs/NRT, and continued use of ONPs/NRT. During the Observation Phase, ONP participants will (H3a) have higher rates of abstinence from cigarettes, (H3b) use their study product for a greater number of days, and (H3c) be more likely to purchase their study product than participants in the NRT group. With stubbornly high rates of smoking—and consequently lung and oral cancers—existing approaches have been inadequate and cannot be the sole means to reduce smoking in rural Appalachia. We propose to evaluate the effectiveness of a potentially reduced harm tobacco product, ONPs, which has significant appeal to rural Appalachian smokers. With expertise conducting remote, large-scale switching trials, our team is uniquely suited to conduct this investigation. This urgently needed and innovative study will be critical for public health officials, regulators, and healthcare providers working to reduce cancer disparities in rural Appalachia.

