## Switch Phase

The Switch Phase will start on a participant’s “switch date” and will last for 12 weeks. Study participants will receive a reminder text the day before and on the day of their Switch Day ***(SD Reminder Text).*** The goal of the Switch Phase is to identify whether there are differences in cigarette smoking patterns (i.e., switching to the study product, abstinence from cigarettes, and frequency of smoking) between the ONP and NRT groups. We will also assess potential differences in subjective measures of product appeal, craving and withdrawal relief, and changes in perceived cigarette dependence between groups.

Switch Phase: Product Sample Survey

The Switch Phase product sample survey will be automatically sent via REDCap 4 weeks after switch day. ***(Product Sample Survey).*** Participants will be asked to complete questions on their study product preferences for nicotine concentration and flavor for their next (and last) product shipment. Study staff will call, email or text (any combination based on participant preferences) participants up to 10 times to remind them to complete the survey if they have not completed it within two weeks. ***(Survey Reminder)***

Switch Phase: Mid-Switch Survey

The Mid-Switch Survey will be self-administered via REDCap 6 weeks after the switch date to assess product appeal, craving and withdrawal, perceived cigarette dependence, and smoking and study product use behaviors; this survey will also include an iCO assessment. ***(Survey Message, Mid-Switch Survey)*** Study staff will call, email or text (any combination based on participant preferences) participants up to 10 times to remind them to complete the survey if they have not completed it within two weeks. ***(Survey reminder).***

Switch Phase: Mid-Switch Phone Call

The Switch Phase Mid-Switch Phone Call will occur approximately 6 weeks after the switch date, after participants have received their product shipment. This call will provide an opportunity to check-in with participants to confirm receipt of their final shipment and answer any product- or study-related questions. Participants will also be reminded about completing the Switch Phase assessment survey that occurs at the end of Switch Phase (12-weeks after switch date). ***(Mid-Switch Phone Call Script)*** If study staff are unable to connect with the participant, the participant will be emailed or texted the information ***(Mid-Switch Email).***

Switch Phase: Post-Switch Survey

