Aim 1: The examination of differential levels of (H1a) switching, (H1b) abstinence from cigarettes, and (H1c) cigarettes smoked per day, between the ONP and NRT study arms at the end of the 12-week Switch Phase will be the focus of Aim 1. Hypotheses 1a-b: Complete switching rates and abstinence from cigarettes will be compared between arms using logistic regression analysis, adjusting for baseline variables as needed. In an exploratory analysis, we will also evaluate whether sex modifies the associations between study group and the switching and abstinence outcomes using product interaction terms (see Section C.11). Hypothesis 1c: If needed, we will apply a normalizing transformation to the number of cigarettes smoked per day (e.g., taking the logarithm) before proceeding with the analysis as a means of removing the effects of potential outliers. We will compare cigarettes smoked per day between the two arms using linear regression analysis. The model will adjust for cigarettes smoked per day at baseline and other baseline variables if they are imbalanced.

Aim 2: The focus of Aim 2 is the examination of (H2a) product appeal and (H2b) cigarette craving and nicotine withdrawal at the end of the Switch Phase and (H2c) among complete switchers, change in cigarette dependence from baseline to the end of the Switch Phase between the study arms. Hypothesis 2a: We will examine differences in product appeal between the ONP and NRT arms at the end of the Switch Phase with linear regression models. These models will be adjusted for potential confounders including baseline variables such as age, gender, number of cigarettes smoked per day, and/or randomization stratification factors as necessary; normalizing transformations will be employed if needed. Hypothesis 2b: Similar to hypothesis 1a, the analysis of cigarette craving and withdrawal symptoms will be evaluated with linear regression models adjusting for appropriate confounders. Hypothesis 2c: Among participants who completely switched to their assigned study product, change in nicotine dependence from baseline will be compared between smoking abstainers in the ONP and NRT arms using linear regression analysis, adjusting for baseline nicotine dependence and other variables as outlined in Hypothesis 2a.

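### H2b predicts a greater reduction in craving and withdrawal, but is analysed on the week-12 score alone, with no baseline score named, week 6 left out, and about 82% expected not to be abstinent

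*Protocol*

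**What the plan says.** **Hypothesis.** Protocol section 2, Aim 2, predicts under H2b that participants randomised to ONPs will have "greater reduction in craving and withdrawal symptoms than participants randomized to NRT".

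**Analysis.** Section 15, Data Analysis Techniques, Aim 2, gives as the focus "H2b) cigarette craving and nicotine withdrawal at the end of the Switch Phase". The method is that "the analysis of cigarette craving and withdrawal symptoms will be evaluated with linear regression models adjusting for appropriate confounders". The text likens this to hypothesis 1a, which is a logistic model. If 2a was meant, the baseline variables listed there are age, gender, cigarettes per day and stratification factors, with no craving or withdrawal score among them.

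**Data collected.** Section 3, Switch Phase, says: "The Mid-Switch Survey will be self-administered via REDCap 6 weeks after the switch date to assess product appeal, craving and withdrawal". The Post-Switch Survey repeats these measures at week 12. The description of the baseline survey in section 3 does not say whether it carries craving and withdrawal items.

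**Neighbouring hypotheses.** For H2c, "change in nicotine dependence from baseline will be compared between smoking abstainers in the ONP and NRT arms", and the model is specified as "adjusting for baseline nicotine dependence and other variables as outlined in Hypothesis 2a". H1c adjusts for baseline cigarettes per day. H2b has no counterpart to either.

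**Planning rates.** Section 15, Power Analysis, assumes 13% abstinent on NRT and 23% on ONP at week 12, with 400 per arm retained.

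**The concern.** H2b concerns how well the assigned product relieves craving and withdrawal once cigarettes are taken away. The plan tests it on one score, 12 weeks after switch day, in everyone still in follow-up. Most of those people are expected not to be abstinent by then, and cigarettes also relieve withdrawal: in the pilot described under Preliminary Research, participants using two pouch strengths and their usual cigarette "noted similar overall withdrawal relief across products". A low week-12 score can therefore come from the product, from cigarettes or from both. The share of non-abstainers also differs by arm and is itself affected by treatment.

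Two economies are missed as well. The hypothesis is worded as a change, yet no baseline score is named, and the week-6 score plays no part in the H2b comparison. At stake is the interpretability and precision of a secondary hypothesis that carries part of the proposed mechanism for better switching. The primary abstinence outcome is not affected.

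**Working it through.** **1. The plan's own power figure, to confirm the inputs.** The protocol gives no figure for H2b, so the check starts from abstinence. With p1 = 0.13, p2 = 0.23, mean 0.18 and two-sided α = 0.05:

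power = Φ{[0.10 − 1.96·√(2·0.18·0.82/n)] / √[(0.13·0.87 + 0.23·0.77)/n]}

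- n = 400 per arm: (0.10 − 0.0532)/0.0269 = 1.74, giving 95.9% (stated: above 95%).
- n = 350 per arm: (0.10 − 0.0569)/0.0288 = 1.50, giving 93.3% (stated: above 90%).

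Both statements reproduce, so 13%, 23% and 400 per arm are the right inputs for what follows.

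**2. Who is scored at week 12.**

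| | ONP | NRT | Both |
|---|---|---|---|
| Scored | 400 | 400 | 800 |
| Abstinent | 0.23 × 400 = 92 | 0.13 × 400 = 52 | 144 |
| Not abstinent | 308 (77%) | 348 (87%) | 656 (82%) |

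**3. Possible dilution (effect sizes are assumptions).** Suppose the product lowers craving by δ SD in abstainers and by k·δ in non-abstainers. With the average abstinent share of 0.18, and leaving aside the difference in mix between arms, the all-participant effect is δ(0.18 + 0.82k). Power at 400 per arm is Φ(effect/√(2/400) − 1.96), where √(2/400) = 0.0707.

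| δ | Undiluted power | Effect at k = 0 | Power at k = 0 |
|---|---|---|---|
| 0.2 | 81% | 0.036 | 7% |
| 0.3 | 99% | 0.054 | 12% |
| 0.5 | >99.9% | 0.090 | 25% |

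The result depends heavily on k. For δ = 0.3 and k = 0.5, the effect is 0.3 × 0.59 = 0.177 SD and power is Φ(2.50 − 1.96) ≈ 71%. At k = 1 there is no dilution. The protocol gives no information on k.

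**4. Could the sign reverse?** Take an assumed 0–100 scale (lower is better), with ONP abstainers at 25, NRT abstainers at 30 and non-abstainers in both arms at s:

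ONP − NRT = (0.23·25 + 0.77s) − (0.13·30 + 0.87s) = 1.85 − 0.10s

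- s = 15: 17.30 against 16.95, a difference of +0.35 (slightly against ONP).
- s = 18.5: zero.
- s = 25: −0.65 (favours ONP).
- If ONP non-abstainers share the 5-point benefit (10 against 15): 13.45 against 16.95, a difference of −3.5.

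**5. What the baseline score is worth.** Under randomisation the expected baseline means are equal, so the expected arm difference in week-12 level equals the expected arm difference in change. Only the variance differs. Relative to the week-12 score alone (variance 1), with an assumed correlation ρ between baseline and week 12:

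| ρ | Change score, 2(1 − ρ) | Baseline as covariate, 1 − ρ² |
|---|---|---|
| 0.3 | 1.40 | 0.91 |
| 0.5 | 1.00 | 0.75 |
| 0.7 | 0.60 | 0.51 |

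At each ρ shown, the covariate form beats both alternatives. A plain change score is less precise than the week-12 level when ρ is below 0.5.

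**The case against.** The case for leaving the plan alone has real substance.

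- **The contrast is valid.** H2b is worded by randomised group, and comparing everyone by arm answers that. A reader might infer that the endpoint measures relief by cigarettes instead of by ONP or NRT. The document does not support that: 13% to 23% are expected to be abstinent, and people who fail a verified 7-day abstinence criterion may have cut down and may still be using the free product. Nor does non-abstinent mean relapsed, since some may never have stopped. This stands.
- **No reversal is shown.** A reader might infer that the better product would look worse on craving. In the illustration above that needs non-abstainers to score below 18.5 and to get no product benefit. Nothing in the protocol says so, and the pilot is a small study of single product-use visits. This stands.
- **Level against change is not a bias.** Step 5 confirms this. A baseline score is also not excluded by the general adjustment wording, and a separate analysis plan could name it. This stands in part: as written, the protocol adjusts for imbalanced or confounding covariates, which is a weaker ground for including the score than its prognostic value.
- **Week 6 is not wholly unused.** It may enter the missing-data weights as a previous outcome. True, but it has no place in the H2b comparison.
- **Week 12 is the common time point for Aims 1 and 2.** That is a fair reason to keep it. It does not argue against also using a score already collected.
- **An extra survey soon after switch day** would alter a five-assessment schedule with linked payments, and no early abstinence rate is given to show what it would gain. This stands, so the fix does not rely on one.

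**Conclusion.** The point holds as a matter of interpretation and precision. H2b is hypothesised as a reduction but analysed as a single week-12 level, without a named baseline score and without the week-6 data. On the planning rates, 82% of those scored (77% ONP, 87% NRT) are not abstinent. The comparison remains unbiased for the effect of assignment, but it mixes product relief with cigarette relief and probably understates any product-specific effect.

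The 82% rests on the protocol's abstinence rates applying to the 800 retained. The size of the dilution rests on an assumed share of effect in non-abstainers: for a 0.3 SD effect, power runs from 12% (none) through about 71% (half) to 99% (full). The precision lost by omitting baseline is a residual variance of 1.00 instead of 0.75 at an assumed correlation of 0.5. Neither a reversed sign nor bias from omitting baseline is established.

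**What to change.** In section 15, Aim 2, Hypothesis 2b:

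1. Analyse craving and withdrawal with a repeated-measures linear model of the week-6 and week-12 scores, with arm, time, their interaction and the baseline score as covariate. Report the adjusted arm difference at each time, and say that this is how the reduction in Aim 2 is estimated.
2. First confirm that the baseline survey carries the same craving and withdrawal items.
3. Show scores by current smoking status and arm at each time, labelled descriptive and non-randomised because smoking status arises after randomisation.
4. State that the arm comparison estimates the effect of assignment, with concurrent smoking included, and does not isolate relief by the product.
5. Correct the cross-reference to hypothesis 1a, which is a logistic model.

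The cost is a few lines of text and slightly more analysis work. If the baseline survey already has the items, no new data are needed, and the primary outcome and sample size are unchanged. A short survey about a week after switch day is optional and not needed for this fix.

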**Data Analysis Techniques**

Power Analysis: Biochemically verified 7-day point prevalence abstinence from cigarettes at the end of the 12- week Switch Phase by study arm (ONP, NRT) is the primary outcome of the study and was chosen because it is a critical outcome to inform public health interventions and potential FDA regulations of ONPs. It is also stringent statistically, requiring a sample size that will provide sufficient statistical power to examine the other study outcomes. Although we will not biochemically confirm use of NRT or ONP, biochemical verification of abstinence from cigarettes combined with self-reported use of NRT or ONP is indicative of complete switching. To derive our NRT arm abstinence estimate of 13% we used our prior trial that investigated the effects of NRT sampling on cessation outcomes.^70^ Crucially, this trial included a sample of rural participants; in this rural subsample, the cessation rate was 13%.^70^ We derived our ONP arm estimate of 23% based on our preliminary data. As the goal of that study was not switching, we believe this estimate to be conservative. Assuming 80% retention at the end of the 12-week Switch Phase, a total sample of 800 participants (400 per arm), will provide greater than 95% power to detect a difference in smoking abstinence between the NRT and ONP arms for a two-sided, α=0.05 level chi-squared test. Further assuming 70% retention at the end of the 14-week Observation Phase, a sample of 700 (350 per arm) will provide over 90% power to detect a significant difference between the ONP and NRT arms.

Data Analytic Plan: Statistical analyses will be performed using SAS 9.4. P-values less than 0.05 will be considered statistically significant. Baseline demographics and smoker characteristics will be summarized by arm (ONP and NRT), as appropriate. Continuous variables will be presented as mean ± standard deviation and compared between the arms with t-tests. Categorical variables will be presented as frequencies and proportions and compared with chi-squared tests. Balance of all covariates according to randomization will be confirmed prior to conducting the below analyses. Any imbalanced covariates will be controlled for in regression models.

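### H2c compares dependence between arms only among complete switchers, a post-randomisation group expected to differ by arm: the contrast is not randomised, and the general power statement does not cover it

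*Protocol*

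**What the plan says.** Section 2 of the protocol (Aim 2) states a directional hypothesis in a restricted population: "H2c: Among complete switchers, ONP participants will report greater reductions in cigarette dependence than NRT participants". Section 15 (Data Analysis Techniques, Hypothesis 2c) carries the restriction into the analysis: "Among participants who completely switched to their assigned study product, change in nicotine dependence from baseline will be compared between smoking abstainers" in the two arms. The method is linear regression, "adjusting for baseline nicotine dependence and other variables as outlined in Hypothesis 2a".

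Aim 1 in section 2 defines the restricting variable and predicts that it differs by arm. In the ONP group the plan expects "the highest rates of (H1a) complete switching (cigarette abstinence + study product use").

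The power analysis in section 15 concerns abstinence only. It assumes 13% on NRT ("To derive our NRT arm abstinence estimate of 13% we used our prior trial") and 23% on ONP ("We derived our ONP arm estimate of 23% based on our preliminary data"), with 400 retained per arm. It also describes the primary outcome as stringent, "requiring a sample size that will provide sufficient statistical power to examine the other study outcomes".

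The missing-data paragraph of section 15 plans inverse probability weighting from a model for missingness. In the Aim 1 and Aim 2 analyses only the sex-interaction analysis is called exploratory; H2c is not.

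**The concern.** H2c conditions on something the assigned product is expected to change. If ONPs move 23% of smokers off cigarettes and NRT moves 13%, the ONP switchers probably include people who would not have switched on NRT. The two groups may then differ in how hard they find it to stop, in motivation, or in other traits that also bear on dependence at week 12. A difference between them, or its absence, could come from who switched and not from the product.

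Neither planned safeguard reaches this. Regression on baseline dependence and other baseline variables removes what those variables capture and nothing else. The weighting deals with people whose data are missing; a participant who answers the week-12 survey and still smokes is not missing, but is outside H2c.

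The second issue is sample size. The assurance about the other outcomes is tied to a calculation with 400 per arm, and H2c uses a small fraction of them.

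The restriction is written into the objectives, so an analysis plan that implements them would inherit it.

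**Working it through.** **Inputs.** From section 15: abstinence 13% (NRT) and 23% (ONP), 400 retained per arm at week 12 (80% of 1,000), two-sided alpha 0.05. The protocol gives no SD, target difference or power for dependence, so differences below are in SD units.

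**The plan's own figure.** Pooled rate 0.18. SE under the null = √(2 × 0.18 × 0.82 / 400) = 0.0272. SE under the alternative = √((0.13 × 0.87 + 0.23 × 0.77) / 400) = 0.0269. Power = Φ((0.10 − 1.96 × 0.0272) / 0.0269) = 95.9%. With 350 per arm it is 93.3%. The stated values (above 95% and above 90%) reproduce.

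**People available for H2c.**
- NRT: 0.13 × 400 = 52. ONP: 0.23 × 400 = 92. Total 144 of 800, or 18%.
- This is an upper limit at planned retention, because a complete switcher must also be using the study product.

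**Detectable difference at 80% power**, (1.960 + 0.842) × √(1/n₁ + 1/n₂):

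| Set | NRT | ONP | SD units |
|---|---|---|---|
| All retained | 400 | 400 | 0.20 |
| All abstainers, no dropout | 65 | 115 | 0.43 |
| All abstainers at 80% retention | 52 | 92 | 0.49 |
| 80% of abstainers use product (assumed) | 42 | 74 | 0.54 |
| 50% of abstainers use product (assumed) | 26 | 46 | 0.69 |

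For 52 and 92, √(1/52 + 1/92) = 0.173, and 2.802 × 0.173 = 0.49.

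**Power for H2c with 52 and 92:**

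| True difference (SD) | Unadjusted | Adjusted, baseline correlation 0.5 (assumed) |
|---|---|---|
| 0.2 | 21% | 27% |
| 0.3 | 41% | 52% |
| 0.4 | 64% | 76% |
| 0.5 | 82% | 91% |

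**Illustration of selection (assumed model).** Each person has a latent difficulty trait, standard normal, with the same distribution in both arms. Switchers are the lowest 13% on NRT and the lowest 23% on ONP. The product has no effect on dependence.
- Mean of the lowest fraction p is −φ(z_p)/p.
- NRT switchers: −1.627. ONP switchers: −1.320. Gap: 0.307 SD.
- The spurious outcome difference is the correlation times the gap: 0.3 × 0.307 = 0.09 SD; 0.5 × 0.307 = 0.15 SD.
- In this model ONP switchers have the higher difficulty. If difficulty goes with more dependence, the bias works against H2c. Other selection mechanisms could reverse it.

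**The case against.** **A subgroup question can be legitimate.** H2c asks about people who switched. A comparison in everyone randomised would mix in continuing smokers and largely restate the effects on abstinence and cigarettes per day. This stands in part. It is a reason to keep the switcher comparison, but not to treat it as a randomised test.

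**No power is claimed for H2c.** This stands. A reader might infer that H2c is underpowered or that a stated power is wrong. The documents do not support that: there is no SD or target difference, unadjusted power is 82% at 0.5 SD, and baseline adjustment may raise it. What can be said is that an assurance built on 400 per arm does not transfer to about 144 people.

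**The bias is modest and may run the other way.** This also stands. With a standard error of about 0.17 SD, a 0.10 SD bias raises the two-sided rejection rate from 5% to about 9%, and in the assumed model almost all of that lies opposite to H2c. The illustration does not show a spurious ONP benefit. The loss of randomised protection does not depend on it.

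**Wording.** A reader might infer that naming both switchers and abstainers in one sentence creates two analysis sets. It does not: every complete switcher is by definition abstinent, so the second term is redundant. The outcome label does slip, from cigarette dependence in the aims and the survey descriptions to nicotine dependence in the H2c analysis.

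**Floor effect.** One might also expect dependence scores to sit near their minimum in verified abstainers. The protocol does not name the scale for H2c, so this cannot be established.

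**Conclusion.** The point holds in limited form. H2c is a between-arm contrast in a group formed by a post-randomisation outcome that the trial expects to differ by arm. It is not a randomised comparison, and the planned adjustment and weighting do not make it one. This follows from the protocol's own definitions and rates.

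The size of any bias is uncertain: 0.09 to 0.15 SD under the stated latent-trait model and correlations of 0.3 to 0.5, with the direction open. The detectable difference is about 0.49 SD unadjusted, against 0.20 SD for an outcome analysed in all 800 retained, so the general power statement does not extend to H2c.

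The documents do not show that H2c is underpowered, nor that the switcher comparison must be removed. The primary outcome and its power calculation are unaffected. This is a weakness in one hypothesis under Aim 2 that should be corrected.

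**What to change.** 1. Add, as the randomised test under H2c, a comparison by arm of cigarette dependence at week 12 in the full intent-to-treat sample: ANCOVA on baseline score and the stratification factors, with the missing-data methods already stated.
2. Keep the complete-switcher comparison, labelled exploratory and non-randomised, and report it without causal wording.
3. Use cigarette dependence as the outcome term throughout H2c.
4. Limit the sentence about sufficient power for other outcomes to those analysed in all retained participants.

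The cost is the wording of H2c and a paragraph of analysis. No new data are needed, because the Post-Switch Survey (section 3) already measures perceived cigarette dependence in both arms at 12 weeks. The drawback is that the comparison of everyone randomised includes continuing smokers. It answers a somewhat different question and partly reflects the abstinence effect, which is why the switcher comparison is worth keeping beside it.
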